#### Inclusion criteria

(1) participants who meet the aforementioned diagnostic criteria;(2) consciousness, stable vital signs, and ability to understand and follow the instructions. Barthel Index (BI) > 20 (Mahoney and Barthel, 1965), FMA (0–95), Mini-mental State Examination (MMSE) meet the following criteria: illiteracy > 17, primary school level > 20, secondary school level (including technical secondary school) > 22, and college-level (including junior college) > 23 points;(3) 25 ≤ age ≤ 85, regardless of gender;(4) first episode of stroke;(5) depression level as mild or moderate (HAMD scores ≥ 7 and ≤ 24);(6) the course of the disease is limited to 2 weeks to 36 months after the stroke; and(7) participants can understand the study protocol and provide written informed consent.

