**Methods:**

This multicenter, prospective, randomized, controlled study aims to form a set of effective clinical treatment schemes that integrate TCM, Western medicine, and rehabilitation for PSD. A total of 202 participants recruited from four centers will be randomized into either the integrative medicine or standard care group. Standard care—basic treatment, general nursing care, and exercise therapy—will be provided to all participants. The integrative medicine group will also receive acupuncture, Chinese herbs, and repeated transcranial magnetic stimulation (rTMS). Participants will receive acupuncture and rTMS treatments five times per week for 4 weeks and will be administered Chinese herbs, basic treatment, general nursing care, and exercise therapy for 4 weeks. The primary outcomes include the Hamilton Depression Scale (HAMD), Self-Rating Depression Scale (SDS), and Activity of Daily Living Scale (ADL). And the secondary outcomes include the Montreal Cognitive Assessment Scale, the Fugl-Meyer Assessment (FMA) Scale, and the Pittsburgh Sleep Quality Index (PSQI). All outcome measures will be evaluated at baseline, week 4 (the end of the treatment courses), and week 8 (the end of follow-up). Safety assessments will be performed throughout the study.

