**Patients**
Screening	×						
Informed consent	×						
Demographic data		×					
Disease history		×					
Randomization		×					

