### Randomization and allocation

The randomization method for this study is a central randomization system. An external statistician will use randomizer software (SPSS software version 25.0) to generate a table of random numbers. Applications for random numbers can be made *via* text messages or phone calls. The applicant will call the randomization center and then enter the subject information in the voice form or send the subject information to the randomization center by SMS. After the central randomization system receives the application information, the patient's randomization number and the group will be returned, and the applicant will receive the randomization assignment email. Grouping information will be hidden using sequentially numbered, opaque, and sealed envelopes to achieve allocation concealment.

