### Statistical analysis

Statistical analyses will be carried out by statisticians unaware of the groupings. The statistical analysis will be performed using SPSS software version 25.0. A two-sided 5% significance level will be adopted, and the corresponding 95% CI will be calculated to the greatest extent possible. A *p*-value of <0.05 will be set as the significance level.

Demographic characteristics and baseline measurements of the variables in each group will be summarized. Measurement data that conform to a normal distribution will be displayed using the mean ± SD, while the median, minimum, and maximum will describe measurement data that do not conform to a normal distribution. To assess the treatment effectiveness, outcome measurement data at baseline, after the intervention, and follow-up (i.e., 4 and 8 weeks), will be analyzed. For the qualitative data, the difference between and within groups will be tested by the chi-square or Fisher's exact test. For quantitative data, either parametric tests (Student's *t*-test) or non-parametric tests (Mann–Whitney *U*-test, Wilcoxon signed-rank test) will be used, depending on the normality of the distribution. In addition, the intention-to-treat analysis will be carried out to minimize potential attrition bias.

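### Patients enter from 2 weeks to 36 months after stroke, but the stated between-group tests carry no covariate, so variation due to time since stroke stays in the error term and chance imbalance in it goes uncorrected.

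*Protocol article*

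**What the plan says.** Under Inclusion criteria, item 6, "the course of the disease is limited to 2 weeks to 36 months after the stroke". Thirty-six months is about 156 weeks, so the longest permitted interval is some 78 times the shortest. Item 2 also admits a wide range of motor function (FMA 0-95).

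Under Statistical analysis, for quantitative outcomes "either parametric tests (Student's *t*-test) or non-parametric tests (Mann–Whitney *U*-test, Wilcoxon signed-rank test) will be used", "depending on the normality of the distribution". Of these, the t-test and the Mann-Whitney test can compare the arms; the signed-rank test is for paired data. No covariate is named. Baseline data have a descriptive role only: "Demographic characteristics and baseline measurements of the variables in each group will be summarized".

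ADL is one of three primary outcomes; FMA and MoCA are secondary. Table 1 lists "Disease history" among the baseline items, and the interval since stroke must be known for each patient to apply criterion 6. The entry window is not among the limitations in the Discussion.

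**The concern.** If patients a few weeks after stroke are still improving without treatment while patients two or three years out are largely stable, the two have different expected 4-week changes whichever arm they are in. A t-test or rank test treats that difference as noise. Two consequences follow: wider confidence intervals, and no correction when one arm happens to receive more early patients.

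The baseline score does not fully stand in for this factor. Two patients with the same ADL or FMA at entry, one at 3 weeks and one at 30 months, may be on different slopes. An analysis adjusted only for baseline would leave that part unexplained.

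At stake is the precision of one primary and two secondary outcomes. The article's power calculation covers HAMD only, so ADL has no documented margin to absorb a loss.

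**Working it through.** **1. The plan's own figure.** Sample size calculation, HAMD, difference 2, SDs 3.40 and 4.51, two-sided 5%, 90% power:

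n = (1.96 + 1.28)² × (3.40² + 4.51²) / 2² = 83.72, so 84 per group. This reproduces. The SDs are those of unadjusted pilot scores and match an unadjusted test, so the figure does not depend on the present point. With pooled SD √((3.40² + 4.51²)/2) = 3.99, the planned effect is 2/3.99 = 0.50 SD.

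**2. Chance imbalance.** If nothing balances the arms on a baseline factor, its standardised difference between arms has standard error √(2/n).
- n = 101 (enrolled per arm): √(2/101) = 0.141; probability of a difference above 0.25 SD in either direction, 7.6%.
- n = 84 (evaluable per arm): √(2/84) = 0.154; probability 10.5%.

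**3. Assumptions for size.** The documents give no distribution of time since stroke, and no SD or explained variance for ADL, FMA or MoCA. Assume an early-phase share p of 0.3 to 0.5, and an extra 4-week change g in early-phase patients of 0.4 to 1.2 residual SDs, where residual means after adjustment for baseline.

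**4. Imbalance in the early-phase share**, 95% limit, 101 per arm: 1.96 × √(2p(1−p)/101).
- p = 0.3: 12.6 percentage points. p = 0.5: 13.8 points.
- Shift in the observed difference at that limit: 0.126 × 0.4 = 0.05 to 0.138 × 1.2 = 0.17 residual SD.

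**5. Variance and power in a baseline-adjusted model.** Omitting the factor multiplies residual variance by 1 + p(1−p)g².
- Low: 1 + 0.21 × 0.16 = 1.03. High: 1 + 0.25 × 1.44 = 1.36.
- A comparison with 80% power without the factor has z = 1.96 + 0.84 = 2.80. With it, power is Φ(2.80 × √1.03 − 1.96) = 81% to Φ(2.80 × √1.36 − 1.96) = 90%.

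**6. Against the tests actually planned.** These use raw scores, so the yardstick in step 5 is too small. Assume a baseline-to-follow-up correlation of 0.8, and time since stroke unrelated to the baseline score. Residual variance is then 1 − 0.8² = 0.36 of the raw variance.
- Contribution of time since stroke: 0.36 × 0.034 = 0.012 to 0.36 × 0.36 = 0.13, or about 1-13% of raw-score variance.
- Power from 80%: Φ(2.80 × √1.012 − 1.96) = 80.5% to Φ(2.80 × √1.13 − 1.96) = 85%.
- The shift in step 4 becomes 0.05 × 0.6 = 0.03 to 0.17 × 0.6 = 0.10 raw SD.

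**The case against.** **The unadjusted test is valid.** Its standard error already contains the variance due to time since stroke, and chance imbalance is already covered by the 5% error rate. This stands. The wider interval and the possible imbalance are two views of one loss of precision and must not be added together. A reader might infer that early recovery biases the treatment comparison; random allocation rules that out in expectation.

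**Allocation may already use the factor.** A reader might infer that randomisation ignores time since stroke, because the article says only that "An external statistician will use randomizer software (SPSS software version 25.0) to generate a table of random numbers" and names no balancing factor. The documents do not support that inference. The article describes a central system that receives subject information before returning a group, and a condensed article may leave strata to the full protocol. No claim about randomisation is made here. The named tests would not use the factor even if allocation did.

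**The analysis plan may add covariates.** It may, but the article does more than stay silent: it names tests that cannot carry a covariate and makes normality the only criterion for choosing between them.

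**The inputs are assumed, and the low end is trivial.** This stands. Only hospitalised patients are recruited, so the mix may be lopsided: at 85% early-phase, p(1−p) is 0.13 rather than 0.25. The upper figures (36%, 90% power) hold only relative to a baseline-adjusted model. Under the plan as written, the missing baseline adjustment is probably the larger loss.

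**HAMD, the outcome that sizes the trial, is not shown to be harmed.** This stands.

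**Conclusion.** The point holds as one of precision. A factor with a very wide permitted range, already established for each patient at eligibility, goes unused because the stated tests cannot use it.

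The loss cannot be read from the documents. Under the assumed ranges it is about 3-36% of residual variance relative to a baseline-adjusted model, and about 1-13% of raw-score variance relative to the planned tests (correlation 0.8 assumed). The low end is negligible and the high end moderate. That ADL, FMA and MoCA are the scales most affected is also an assumption about recovery after stroke, not something the article shows.

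It would go too far to read this as an invalid primary comparison, a wrong HAMD sample size or a defect in allocation. The case for acting is that adjustment costs little if specified in advance, whereas adding the covariate after an imbalance is seen would be open to challenge.

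**What to change.** Before unblinded analysis, replace the two-sample tests for the between-group comparison of ADL, FMA and MoCA, and of HAMD for consistency, with an ANCOVA or a mixed model. Include the baseline score and time since stroke as covariates, the latter as log months or as two groups with one cut-point fixed in advance.

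Apply the model at the visits where each scale is measured. That must first be settled for FMA and MoCA: the Secondary outcomes section says that the secondary outcome is measured at week 8, but Table 1 shows no week-8 mark for either scale. The two need to be reconciled.

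The cost is one more model term and a model-based test in place of a simple one, with its assumptions to check. No new data should be needed. No change to randomisation is needed: with about 100 patients per arm, covariate adjustment alone recovers nearly all the precision that stratification would give.

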#### Exclusion criteria

(1) patients with acute brain trauma, brain infection, effusion, or tumor occupation;(2) there are intracranial metals and other foreign bodies (such as orthopedic materials, arterial clips, etc.), cardiac pacemakers, deep brain stimulators, and other electronic devices;(3) patients with previous seizures, including primary and secondary seizures;(4) patients with severe complications of the cardiovascular system, liver, kidney, or a psychiatric history;(5) there is a significant cognitive impairment [MMSE: illiteracy ≤ 17, primary school level ≤ 20, secondary school level (including technical secondary school) ≤ 22, and college-level (including junior college) ≤ 23 points] or hearing impairment, aphasia;(6) patients have coma, terminal illness, or acute exacerbation of chronic disease;(7) patients who have taken psychotropic drugs or have already been treated for depression for nearly a month; and(8) people with unstable vital signs or patients with other mental disorders.

#### Discontinuation criteria

(1) serious adverse reactions have occurred during the study;(2) subjects develop serious complications or other serious diseases during the study, and emergency measures are needed; and(3) the subject is unable to continue the study for other reasons.

#### Patient recruitment

In this RCT, we will recruit hospitalized patients from acupuncture departments, rehabilitation departments, and neurology departments in four trial centers, which are the Third Affiliated Hospital of Zhejiang Chinese Medical University, Hangzhou Hospital of Traditional Chinese Medicine, the Second Hospital of Jinhua, and Zhejiang General Hospital of Armed Police.

### Randomization and allocation

The randomization method for this study is a central randomization system. An external statistician will use randomizer software (SPSS software version 25.0) to generate a table of random numbers. Applications for random numbers can be made *via* text messages or phone calls. The applicant will call the randomization center and then enter the subject information in the voice form or send the subject information to the randomization center by SMS. After the central randomization system receives the application information, the patient's randomization number and the group will be returned, and the applicant will receive the randomization assignment email. Grouping information will be hidden using sequentially numbered, opaque, and sealed envelopes to achieve allocation concealment.

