**Intervention**
Integrated rehabilitation group (*n* = 101)			Acupuncture TCM rTMS add the same treatment of the standard care group				
Standard care group (*n* = 101)			Basic disease treatment General care Exercise therapy				

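### The article describes two allocation routes, a central phone/SMS reply and sealed numbered envelopes, and does not say which one governs

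*Protocol article*

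**What the plan says.** The Randomization and allocation section sets out these steps, in this order:

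- The method: "The randomization method for this study is a central randomization system".
- The sequence: "An external statistician will use randomizer software (SPSS software version 25.0) to generate a table of random numbers".
- The request: "Applications for random numbers can be made *via* text messages or phone calls".
- The reply, once the subject's details have been received: "the patient's randomization number and the group will be returned, and the applicant will receive the randomization assignment email".
- Concealment: "Grouping information will be hidden using sequentially numbered, opaque, and sealed envelopes to achieve allocation concealment".

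The section does not mention blocks, strata or centre, and it does not call the list simple or unrestricted. The abstract gives 202 participants from four centres, and Table 1 plans 101 per group. Table 1 puts screening and informed consent at W-1. Randomization and the baseline scales both stand at W0, with no order between them. The Blinding section says that operators and participants cannot be blinded, while outcome assessors and analysts will not know the grouping. The Statistical analysis section compares groups by Student's t-test or the Mann–Whitney U-test, with no centre term.

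**The concern.** Concealment means that whoever decides on enrolment cannot know the next assignment. The text describes a central system that could achieve this and then credits concealment to something else. Site staff reading the section could not tell whether a patient's group comes from the central reply or from the next envelope, or what to do if the two disagree.

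What is at stake is selection bias at entry, and several features of this trial make that worth guarding against:

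- Staff delivering treatment see past assignments.
- Patients come from acupuncture, rehabilitation and neurology departments (Patient recruitment), where staff may have a preference between the arms.
- Part of eligibility is judgement: tongue, pulse and symptom pattern (Diagnostic criteria).
- Eligibility also depends on a HAMD score, and the first HAMD marked in Table 1 falls in the same column as randomization.

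Blinded outcome assessment does not repair a bias in who was enrolled into which arm.

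**Working it through.** **1. The two routes side by side**

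| | Central reply | Envelopes |
|---|---|---|
| When the group becomes known | After the subject's details are received | Not stated |
| Who learns it | The applicant, with an email following | Not stated |
| Who holds the assignments beforehand | The randomization center | Not stated |
| Role given in the text | Returns number and group | Achieves concealment |

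There are three ways to read this:

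- *The central reply governs.* The next assignment is unknown until registration, so concealment is already achieved and the envelope sentence describes nothing that is needed.
- *The envelopes govern.* Assignments exist in physical form before patients are registered. Concealment then depends on where the envelopes are kept and whether they are opened in sequence. The opening statement that the method is central is incomplete.
- *The envelopes are a backup, or carry the central result.* This is coherent, but the text does not say it.

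No other section settles which reading is meant.

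**2. What can be said about arm and centre balance**

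The plan's own figure comes first (inputs from Sample size calculation): n = (1.96 + 1.28)² × (3.40² + 4.51²) / 2² = 10.4976 × 31.9001 / 4 = 83.72, so 84 per group. Then 84 × 1.2 = 100.8, so 101 per group and 202 in total. This agrees with Table 1.

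Now *assume*, since the article does not say so, that the list is unrestricted 1:1. With X the size of one arm, X ~ Binomial(202, 0.5):

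- P(X = 101) = C(202,101) / 2²⁰² = 5.6%.
- P(94:108 or worse) = 2 × P(X ≤ 94) = 36%.
- The central 95% range for one arm is 87 to 115.

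Centre sizes are not given. *Assuming* about 50 per centre, P(20:30 or worse in one centre) = 2 × P(Binomial(50, 0.5) ≤ 20) = 0.203. For at least one of four centres it is 1 − (1 − 0.203)⁴ = 0.596, about 60%. Taking 60:40 or worse as the criterion, sizes of 50/50/51/51 give 55% and sizes of 80/60/40/22 give 60%.

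The power cost of overall imbalance is Φ(2 / √(4.51²/n_standard + 3.40²/n_integrative) − 1.96):

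| Analysed | Standard : integrative | Power |
|---|---|---|
| 202 | 101:101 | 94.5% |
| 202 | 94:108 | 94.0% |
| 202 | 87:115 | 93.3% |
| 202 | 115:87 | 94.9% |
| 168 | 84:84 | 90.1% |
| 168 | 71:97 | 88.1% |
| 168 | 97:71 | 90.6% |

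At the unfavourable 95% limit the loss is 94.5 − 93.3 = 1.2 points with all 202 analysed, and 90.1 − 88.1 = 2.0 points with 168.

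**The case against.** Sealed, opaque, numbered envelopes are a recognised concealment method, and foreknowledge would need tampering or a breach of sequence. The text does not say that they are held at the sites or filled in advance there. They may be a backup or a means of passing on the central result. All of this stands, so the risk is possible and not demonstrated. It does not remove the need to say which route governs: the article prints both mechanisms, so this is not detail lost in condensing a fuller protocol.

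A reader might go further and infer from "to generate a table of random numbers" that randomization is simple, so that 101:101 and balance within centres will fail. The documents do not support that. A table of random numbers can be built with blocks or fixed totals, either of which can deliver 101:101. A condensed article may leave blocks and strata to the full protocol. No section promises centre balance, so nothing is contradicted there. Chance imbalance under valid randomization is not systematic bias, and the Interventions and Quality control sections plan standard procedures, training and centre visits to limit differences between sites.

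**Conclusion.** The point holds as an unreconciled description of allocation that should be corrected. The central reply and the envelopes cannot both be the operative source of concealment as written, and the article does not define how they relate. The consequence is a possible, avoidable route to foreknowledge in a trial whose operators and participants are unblinded. The documents give no basis for putting a number on it.

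The figures of 5.6%, 36% and about 60% are correct only if the list is unrestricted, and the last also needs about 50 patients per centre. They do not show that 101:101 or centre balance fails. Even on that assumption, overall arm imbalance costs only about 1 to 2 points of power at the unfavourable 95% limit. Centre stratification and adjustment are therefore inexpensive improvements and not the repair of a demonstrated error.

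**What to change.** Amend the Randomization and allocation paragraph:

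- Name the central system as the sole source of allocation. State that it releases a group only after consent, eligibility and baseline scales are recorded, and make the W0 order explicit in Table 1.
- Delete the envelope sentence. If envelopes are needed, describe them as a backup, kept away from recruiting staff, and say when they may be opened and by whom.
- State whether the list is restricted. If it is not, have the external statistician generate randomly varying permuted blocks stratified by centre for patients not yet randomised.
- In Statistical analysis, include centre in the primary comparison in place of the unadjusted test.

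The first two changes cost a few sentences. The third adds a centre-stratified list to maintain and some predictability within blocks, because staff know past assignments; varying the block size reduces this but does not remove it. The fourth changes the model specification and needs no data beyond the recruiting centre.

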### Blinding

Although unable to blind the intervention operators and participants due to the unique nature of the complex interventions in our trial, the operators, outcome assessors, and statistical analysts will be separated and performed by respective specially-assigned persons, thereby ensuring blinding principles during the process of our clinical trial. The outcome measurement and statistical analyses will be carried out by specially designated researchers who do not know the grouping to avoid possible bias as much as possible.

### Sample size calculation

The data statistician will carefully compute the appropriate sample size for each group based on the difference in postintervention HAMD scores between the two groups. According to our unpublished pilot study, the HAMD score (mean ± standard deviation) in the standard care group was 16.5 ± 4.51, and the HAMD score in the integrative medicine group was 14.5 ± 3.40. The mean HAMD score in the integrative medicine group was 2 points lower than that in the standard care group. Based on a 5% false-positive error rate (α = 0.05, two-sided, the normal distribution quantile table shows that *Z*_1−α/2_ = 1.96) and 90% power (β = 0.1, the normal distribution quantile table shows that *Z*_1−β_ = 1.28), the sample size is estimated as follows:

$$\begin{array}{l} \begin{array}{l} n=\frac{{\left(Z_{1-\alpha /2}+Z_{1-\beta }\right)}^{2}\times (\sigma_{1}^{2}+\sigma_{2}^{2})}{\delta^{2}}\\ \;=\frac{{\left(1.96+1.28\right)}^{2}\times (3.40^{2}+4.51^{2})}{2^{2}}\approx 83.72 \end{array} \end{array}$$

Each group needs to include 84 participants. Assuming an ~20% dropout rate, a total of 202 participants will be enrolled in this trial.

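### The planned 202 participants correspond to a dropout allowance of about 17%, not 20%; if 20% of outcomes are lost, about 81 per group remain rather than 84 and power is about 89%

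*Protocol article*

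**What the plan says.** The Sample size calculation section sizes the trial on the difference in post-intervention HAMD between the two groups.

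- **Error rates:** "Based on a 5% false-positive error rate (α = 0.05, two-sided", with "90% power (β = 0.1".
- **Pilot data:** "the HAMD score (mean ± standard deviation) in the standard care group was 16.5 ± 4.51"; for the integrative arm the pilot mean is 14.5, with an SD of 3.40.
- **Target difference:** "The mean HAMD score in the integrative medicine group was 2 points lower than that in the standard care group".

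The printed formula gives 83.72. The section then concludes: "Each group needs to include 84 participants. Assuming an ~20% dropout rate, a total of 202 participants will be enrolled in this trial".

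Table 1 confirms equal allocation. It lists "Integrated rehabilitation group (*n* = 101" and the same number for the standard care group. The Methods part of the abstract repeats the total of 202. The article does not show how 84 per group became 202 in total.

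**The concern.** A dropout rate is a fraction of those enrolled. If 84 per group must remain after a 20% loss, the number to enrol is 84 divided by 0.8. The stated total is smaller than that, so three planning figures do not agree with one another: the 84 needed per group, the 20% dropout and the 202 enrolled.

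Sample size, dropout and power are figures that readers take from a protocol at face value. A reader of this section would conclude that the trial keeps its 90% power with one participant in five lost. Under the protocol's own inputs, it falls slightly short of that.

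**Working it through.** **Inputs**, all from the Sample size calculation section except the last:

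- two-sided α = 0.05 (Z = 1.96) and 90% power (Z = 1.28)
- δ = 2 HAMD points
- SDs 4.51 (standard care) and 3.40 (integrative medicine)
- dropout about 20%, total 202
- 101 per group (Table 1)

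**Step 1: reproduce the 84.** The sum of variances is 3.40² + 4.51² = 11.56 + 20.34 = 31.90.

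n = (1.96 + 1.28)² × 31.90 / 2² = 83.72, or 83.80 with unrounded normal quantiles.

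Both round up to 84 per group, so the protocol's figure is confirmed.

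**Step 2: the dropout allowance.**

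| Route | Per group | Total |
|---|---|---|
| 84 / (1 − 0.20) | 105 | 210 |
| 84 × (1 + 0.20) = 100.8, rounded up | 101 | 202 |

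The stated total matches the second route exactly. That this route was used is an inference from the numbers. The inconsistency does not depend on it, because it also shows when one works backwards: 101 × 0.80 = 80.8, which is 3.2 below 84.

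**Step 3: the dropout rate that 202 does cover.** 1 − 84/101 = 16.8%. Rounded up, 84 / (1 − d) equals 101 only for d above 16.0% and up to 16.8%.

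**Step 4: power.** Normal formula: power = Φ(2 / √(31.90/n) − 1.96). At n = 80.8, √(31.90/80.8) = 0.628, 2/0.628 = 3.183, and Φ(3.183 − 1.96) = Φ(1.223) = 88.9%. The t-test column uses the noncentral t distribution with pooled degrees of freedom.

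| Evaluable per group | Normal formula | t-test |
|---|---|---|
| 84 (requirement met) | 90.1% | 89.7% |
| 80.8 (101 less 20%) | 88.9% | 88.6% |

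Unequal-variance (Welch) degrees of freedom give 88.5% at 80.8 per group. On either scale the loss relative to 84 per group is about 1 percentage point.

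**Step 5: sensitivity to the dropout rate, with 101 per group enrolled (normal formula).**

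| Dropout | Remaining per group | Power |
|---|---|---|
| 15% | 85.9 | 90.7% |
| 18% | 82.8 | 89.7% |
| 20% | 80.8 | 88.9% |
| 25% | 75.8 | 86.9% |

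**The case against.** The strongest reply is that little is lost and that the loss is conditional. Four points support it.

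- **The rate is approximate.** The protocol marks its 20% with a tilde, and the Quality control section lists measures to keep actual dropout down. At 15% loss, power is above 90%. This stands as a limit on the consequence. It does not reconcile the figures, since an allowance of 16.8% would naturally be described as about 17%.
- **Leaving treatment is not the same as having no outcome.** The Statistical analysis section plans an intention-to-treat analysis, the discontinuation criteria do not say that assessment stops, and follow-up scales are collected by telephone. If some who drop out still have a post-intervention HAMD score, more than 80.8 per group are evaluable. With all 101 per group observed and the same SDs, the formula gives about 94.5%. The article does not describe the handling of missing scores, so this bounds the shortfall without removing it. The 88.9% applies when every dropout lacks the score.
- **The pilot inputs are uncertain.** Error in the SDs or in the 2-point difference probably matters more than three patients per group. That is fair, but it does not excuse an inconsistency that can be corrected by arithmetic.
- **The multiplication by 1.2 is not written down.** This is correct, and it should be presented only as the likely explanation.

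**Conclusion.** The inconsistency is certain and its effect is small. On the protocol's own figures, 202 participants do not leave 84 per group after a 20% loss. They leave about 81, and 210 would be needed. The total is 8 below that (4 per group).

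A reader might go further and infer that the trial is underpowered, or that its 90% power is simply not delivered. The document does not support that. The protocol attaches 90% power to 84 evaluable per group, and 202 provides this up to 16.8% dropout. Even with a full 20% of post-intervention HAMD scores missing, power is 88.9% (normal formula) or 88.6% (t-test).

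These figures assume the protocol's SDs and 2-point difference, equal loss in the two groups, and no contribution to the analysis from participants without a post-intervention score.

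**What to change.** Keep the total of 202 and replace the dropout sentence in the Sample size calculation section with wording such as:

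> 202 participants (101 per group) leave 84 evaluable per group if dropout is at most about 17%; at 20% dropout about 81 per group remain, giving about 89% power.

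The cost is one sentence and a planning figure that reads slightly less favourably. The abstract and Table 1 stay as they are, and no extra patients are needed.

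If the sponsor prefers to keep both the 20% allowance and the 84 per group, the total becomes 210 (105 per group). That means 8 more participants and matching changes in the abstract and Table 1. For a gain of about 1 percentage point in power, the restatement is the proportionate choice.
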